## Abstract

**Background:**

A large number of randomised controlled trials in health settings have consistently reported positive effects of brief intervention in terms of reductions in alcohol use. However, although alcohol misuse is common amongst offenders, there is limited evidence of alcohol brief interventions in the criminal justice field. This factorial pragmatic cluster randomised controlled trial with Offender Managers (OMs) as the unit of randomisation will evaluate the effectiveness and cost-effectiveness of different models of screening to identify hazardous and harmful drinkers in probation and different intensities of brief intervention to reduce excessive drinking in probation clients.

**Methods and design:**

Ninety-six OMs from 9 probation areas across 3 English regions (the North East Region (n = 4) and London and the South East Regions (n = 5)) will be recruited. OMs will be randomly allocated to one of three intervention conditions: a client information leaflet control condition (n = 32 OMs); 5-minute simple structured advice (n = 32 OMs) and 20-minute brief lifestyle counselling delivered by an Alcohol Health Worker (n = 32 OMs). Randomisation will be stratified by probation area. To test the relative effectiveness of different screening methods all OMs will be randomised to either the Modified Single Item Screening Questionnaire (M-SASQ) or the Fast Alcohol Screening Test (FAST). There will be a minimum of 480 clients recruited into the trial. There will be an intention to treat analysis of study outcomes at 6 and 12 months post intervention. Analysis will include client measures (screening result, weekly alcohol consumption, alcohol-related problems, re-offending, public service use and quality of life) and implementation measures from OMs (the extent of screening and brief intervention beyond the minimum recruitment threshold will provide data on acceptability and feasibility of different models of brief intervention). We will also examine the practitioner and organisational factors associated with successful implementation.

**Discussion:**

The trial will evaluate the impact of screening and brief alcohol intervention in routine probation work and therefore its findings will be highly relevant to probation teams and thus the criminal justice system in the UK.

Ethical approval was given by Northern & Yorkshire REC

**Trial Registration number:**

ISRCTN 19160244

## Background

In 2008 in the UK it was estimated that there were approximately 950,000 incidents of alcohol-related violence in the previous year [1]. Alcohol is a factor in nearly half of all violent crimes (defined as assaults, robbery and snatch thefts in which the victim considered the perpetrator to be 'under the influence' of alcohol) [1]. High rates of alcohol and other substance misuse has been found amongst offenders within the prison system in the UK [2-5]. There is therefore strong evidence of an association between alcohol and offending behaviour [4,6,7]. However it is difficult to identify the precise causal relationships between alcohol misuse and offending behaviour [8-10].

The majority of alcohol-related problems in the general population are not due to individuals with alcohol dependence, but to a much larger group of hazardous and harmful drinkers [11]. In the UK, hazardous and harmful drinkers outnumber dependent drinkers by a ratio of 7:1 [11]. Thus, it is clear that the greatest impact in reducing alcohol-related problems at a population level can be made by reducing alcohol consumption in hazardous and harmful drinkers, rather than by focusing on the most extreme cases of alcohol dependence; this is known as the preventive paradox [12]. This present study will help to provide better information into this.

Screening and brief alcohol intervention is an example of secondary prevention [13]; it aims to identify hazardous and harmful drinking at an early stage, before people are consciously aware of the potentially harmful effects of their drinking or are alcohol help seeking, and then deliver advice or counselling to help reduce consumption levels.

### Current evidence on screening and brief interventions

There is a strong evidence-base supporting the effectiveness of brief intervention (BI) in reducing alcohol consumption in adults who are not seeking treatment for alcohol-related problems in a range of health settings. Numerous systematic reviews and meta-analyses have reported beneficial outcomes of brief intervention, compared to control conditions, in terms of reductions in hazardous and harmful drinking [14-23]. However there is a lack of data on the impact of screening and brief interventions within the criminal justice system. Although some studies show promise [24,25], methodological limitations include non-randomised trials and small sample sizes, limiting the conclusions which can be made. A study of offenders in a magistrates' court who had been sentenced for a violent offence committed while intoxicated with alcohol examined re-offending, injury rates and subjects' alcohol-related risk and harm status [25]. Male participants were followed up at three and twelve months post-sentence. Although there was an initial reduction in alcohol use at the 3-month follow up this was not found to be significant [25]. However, there was a significantly lower rate of injury in the offenders who received the intervention compared to those who had not [25].

In summary, there is a need for more research evaluating the impact of screening and brief interventions in the criminal justice system. It is also necessary to ensure that research trials are located in areas with sufficient diversity to be generalisable. In addition, there are key gaps in the evidence-base regarding the cost-effectiveness of brief interventions, the efficiency of screening activity and the optimal methods of brief intervention. Although there have been reported cost-savings in the US in primary care four years post brief alcohol intervention [26] this evidence is lacking in the criminal justice system.

During late 2007 we conducted a pilot study to evaluate the most feasible criminal justice setting to conduct a randomised controlled trial of brief interventions. The main findings of the pilot were:

• The prevalence of individuals with an alcohol use disorder (AUD) in the criminal justice setting is 3 times greater than in the general population.

• The consent rate for study participation, of those eligible, was highest in the probation setting.

• The majority of offenders who were positive on the AUDIT questionnaire [27] reported not feeling coerced to take part in any further research.

• The recruitment, consent and willingness to participate rates were higher in the probation setting.

Of the four settings (probation, prison, police stations and Youth Offending Teams) probation was found to be the most feasible setting to undertake the trial.

## Aim of the study

To evaluate the most efficient and acceptable screening tool to detect hazardous and harmful drinkers in typical probation offices and to evaluate the staff impact and cost effectiveness of different models of brief intervention aimed at reducing excessive drinking in this setting.

## Objectives

The objectives of the trial are:

• To conduct a pragmatic multicentre cluster randomised controlled trial of screening and brief intervention for hazardous and harmful drinkers in typical probation settings in three English regions.

• To identify the most efficient methods for alcohol screening in typical probation settings.

• To compare the effectiveness and cost effectiveness of different models of brief intervention with an information leaflet in offenders with hazardous, harmful and dependent alcohol consumption.

• To assess the implementation of different screening and brief intervention approaches by Offender Managers (OMs) in typical probation practice.

• To identify attitudinal, practical, skill, resource, and reinforcing factors that predict successful implementation of screening and brief intervention in probation settings.

• To assess the relative impact of the different models of screening and brief intervention on uptake of alcohol services, including an alcohol helpline.

• To assess the relative impact of the three intervention strategies on reoffending.

## Methods/Design

### Setting

Ninety-six OMs from 9 probation areas across 3 English regions (the North East Region (n = 4) and London and the South East Regions (n = 5)) will be recruited. All probation offices delivering general probation services in the three regions that do not have current routine screening and brief intervention facilities will be eligible to participate. The study catchment area enables broad population coverage and Randomisation procedures will ensure that offices cover a range of urban and rural areas, socially deprived and affluent communities, traditional communities with relatively stable populations and more urbanized fluid populations, and culturally mixed populations.

### Design

The trial will adopt a 2 × 3 nested factorial design encompassing screening method (the Fast Alcohol Screening Test (FAST) [28] or a modified Single Alcohol Screening Questionnaire (M-SASQ)) [29]) and brief intervention intensity (Client information leaflet (CIL); Brief advice (BA); Brief lifestyle counselling (BLC)). The main advantages of utilising a factorial approach are twofold. First each of the elements (screening tool and intervention) can be analysed independently with sufficient power to make meaningful interpretation of relative effectiveness. Second, the method enables meaningful interpretations of the relative effectiveness of any screening tool and intervention modality.

The 96 recruited OMs will be randomly assigned to 1 of 2 screening tools (48 OMs using each tool) and 1 of 3 intervention conditions (32 OMs in each condition) as shown in Table 1. Since we expect that there may be a difference in uptake of screening between intervention conditions, we expect the recruitment to take varying periods of time in the different conditions.

**Table 1 T1:** SIPS CJS trial design

	Intervention allocation				Total
		**PIL**	**BA**	**BLC**	
	
		OMs = 16	OMs = 16	OMs = 16	OMs = 48
**Screening allocation**	**FAST**	Participants = 80	Participants = 80	Participants = 80	Participants = 240
	
	**M-SASQ**	OMs = 16	OMs = 16	OMs = 16	OMs = 48
		Participants = 80	Participants = 80	Participants = 80	Participants = 240

		OMs = 32	OMs = 32	OMs = 32	OMs = 96
**Total**		Participants = 160	Participants = 160	Participants = 160	Participants = 480

The trial will incorporate cluster randomisation of OMs to avoid the risk of contamination. OMs trained to deliver brief advice become compromised in their ability to deliver alternative versions of such care; thus it is not practical for individual OMs to deliver both control and intervention conditions in this trial. Therefore OMs will consistently deliver one particular type of brief intervention.

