### Study Hypotheses

• Brief lifestyle counselling by an Alcohol Health Worker (AHW) is more effective and cost effective than simple structured advice conducted by OMs in a typical probation setting.

• Brief lifestyle counselling and simple structured advice are more effective and cost effective than a Client Information Leaflet (CIL).

• Access to referral to an AHW results in greater screening and intervention activity than training of probation staff in screening and brief intervention alone.

• Attitudinal, practical skill, resource, and reinforcing factors predict screening and intervention activity.

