### Sample size calculation

The sample size calculation is designed to account primarily for intervention level outcomes. Powering the study in this way will also account statistically for appropriate outcomes for screening approach and screening method. The primary outcome for this study is the proportion of offenders who are consuming alcohol within recommended levels at 6 and 12 month follow-up. Recent meta-analysis [19] suggests that the difference between brief intervention and control is of the order 13%, 5% reduction in the control group and 18% in the brief intervention group. In order to detect a difference of this magnitude at the 5% significance level with 80% power, for a 2-sided test, requires 109 offenders in each of the 3 groups, a total of 327. Our experience with other multi-centre randomised controlled trials of interventions for alcohol use disorders suggests that with assiduous follow-up the potential loss to follow-up across groups is of the order 25%. Taking this loss into accounts inflates the sample required to 145 in each group, a total of 435 offenders.

The proposed study involves a cluster design and requires a statistical adjustment to account for any potential cluster effect. The literature is unclear regarding an appropriate estimation of an intra-class correlation coefficient in this population. Our experience leads us to assume the ICC should be similar to primary care correlation coefficients, 0.04. Assuming a cluster size of the order 3 offenders this inflates the sample size calculation by a factor of 1.1 requiring 160 offenders in each group, a total of 480, with an expectation that at least 365 will be followed up at 12 months.

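### The sample size covers brief intervention against the leaflet only, so the sufficient-power claim is unsupported for brief lifestyle counselling against brief advice

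*Protocol article*

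**What the plan says.** Protocol article, Design: the 2 × 3 factorial layout is justified partly on the ground that "each of the elements (screening tool and intervention) can be analysed independently with sufficient power to make meaningful interpretation of relative effectiveness". Table 1 gives 160 participants and 32 Offender Managers (OMs) per intervention arm.

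Study Hypotheses: the first bullet is that "Brief lifestyle counselling by an Alcohol Health Worker (AHW) is more effective and cost effective than simple structured advice conducted by OMs". The second is that both brief interventions beat the leaflet. The bullets are not labelled primary or secondary.

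Sample size calculation: "The primary outcome for this study is the proportion of offenders who are consuming alcohol within recommended levels at 6 and 12 month follow-up". The effect assumed is given as follows: "the difference between brief intervention and control is of the order 13%, 5% reduction in the control group and 18% in the brief intervention group", tested "at the 5% significance level with 80% power, for a 2-sided test". This gives 109 per group, then 145 after 25% loss, then 160 after a clustering factor of 1.1, with at least 365 of 480 expected at 12 months. No rate is given separately for BA and BLC, and no BLC v BA difference is stated.

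Interventions, Brief lifestyle counselling: clients in this arm also receive the same five-minute advice and the leaflet. The 20-minute session goes to those who attend the appointment.

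**The concern.** The three-arm design poses two kinds of question: whether a brief intervention beats a leaflet, and whether counselling adds anything to brief advice. Only the first has an effect size behind it. Taken literally, the single 18% planning rate for both active arms implies no difference between them.

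The second contrast isolates one added component, because everything else is common to the two arms. The Design section nevertheless claims adequate power for the relative effectiveness of the intervention element without separating the two questions.

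At stake is how a non-significant BLC v BA result is read. A reader who relies on the power claim could take it as evidence that the counselling session adds nothing. For moderate true gains, the sample could easily miss the difference.

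**Working it through.** **Inputs from the protocol article (Sample size calculation, Table 1).** Control 5%, brief intervention 18%; two-sided 5%, 80% power; 25% loss; ICC 0.04; about 3 offenders per OM; 160 per arm; 32 OMs per arm.

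**Inputs assumed.** BA rate 18% (the planning rate applied to this arm), with 10% as a sensitivity value. BLC gains of 5, 10 and 13 points. The document gives none of these for BLC v BA.

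**1. Reproduce the plan's figures.** The two-proportion formula is n = [1.96√(2p̄(1−p̄)) + 0.84√(p₁(1−p₁)+p₂(1−p₂))]² / (p₂−p₁)². With 0.05 and 0.18 it gives 94 per group, and 109 with continuity correction, which matches the plan.
- Loss: 109/0.75 = 145.3, stated as 145.
- Clustering: 1 + (3−1) × 0.04 = 1.08, rounded in the plan to 1.1; 145 × 1.1 = 159.5, stated as 160.

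**2. Effective sample per arm.** Followed up: 160 × 0.75 = 120 (the plan's 365/3 is 121.7).
- Design effect 1.08 (3 per OM): 120/1.08 = 111.1.
- Design effect 1 + (5−1) × 0.04 = 1.16 (5 per OM, from Table 1, 160/32): 120/1.16 = 103.4.

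**3. Power.** Power = Φ[(d − 1.96·s₀)/s₁], where d is the difference, s₀ = √(2p̄(1−p̄)/n) and s₁ = √((p₁(1−p₁)+p₂(1−p₂))/n). The continuity-corrected version replaces d by d − 1/n.

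Example, 18% v 28%, n = 111.1: s₀ = 0.0565, s₁ = 0.0561; (0.10 − 1.96 × 0.0565)/0.0561 = −0.19; Φ = 0.425.

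The table gives the best case (design effect 1.08, uncorrected) and the worst case (1.16, continuity-corrected).

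| Contrast | Best case | Worst case |
|---|---|---|
| Leaflet 5% v brief intervention 18% | 86.4% | 77.9% |
| BA 18% v BLC 23% (+5) | 14.9% | 10.7% |
| BA 18% v BLC 28% (+10) | 42.5% | 33.8% |
| BA 18% v BLC 31% (+13) | 61.7% | 52.1% |

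**4. Gain needed for 80% power (same best and worst cases).**
- BA 18%: 16.4 to 18.2 points.
- BA 10%: 14.1 to 15.8 points.

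**5. Sample needed for 80% power from BA 18%** (uncorrected, 25% loss, factor 1.1): 1,501 per arm for 5 points, 408 for 10 and 251 for 13, against 160 planned.

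**The case against.** Five points on the other side deserve weight.

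- **No effect is stated, so power has no single value.** This stands. A reader might infer that the trial has almost no power for BLC v BA. That fits gains of up to about 5 points from an 18% base, but power is a third or more at 10 points and above one half at 13. The document gives no basis for choosing among them.
- **The 18% on BA is itself an assumption.** This stands. The planning figure is "5% reduction in the control group and 18% in the brief intervention group", with no separate rate for five-minute advice. A lower BA rate reduces the detectable difference, so the figure must be a range.
- **The sentence can be read as a general remark on factorial designs**, namely that each factor is analysed across the other with 160 per intervention arm instead of 80 per cell. This stands in part. But the sentence refers to interpreting relative effectiveness, and a hypothesis in the next section is exactly such a contrast.
- **The calculation matches the stated objective** of comparing brief intervention models with a leaflet, and the hypotheses are unranked. This stands. Being listed first gives BLC v BA no declared priority, and the order of the bullets need not change.
- **Odds ratios with confidence intervals are already planned** (Planned analysis). This stands, and it covers part of the remedy. Nothing in the document says that a non-significant result will be read as no benefit; that is a risk left open by the power claim.

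**Conclusion.** The point holds in a limited form. The power claim in the Design section is supported for each brief intervention against the leaflet (about 78–86% at the planned 18% v 5%) and unsupported for BLC v BA. With 18% assumed on BA, about 120 followed up per arm and a design effect of 1.08 to 1.16, even a further 13 points, as large as the whole assumed effect over the leaflet, gives only about 52–62% power. The gain needed for 80% is about 16.5–18 points, or about 14–16 if BA is 10%.

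Two stronger inferences are not supported. One is that a null BLC v BA result is the most likely outcome even if counselling is better: that depends on the true gain and the BA rate, neither of which is given. The other is a required effect among those who attend the counselling session: that needs an attendance rate, and the document states none. Nor does the point show that the trial is too small for the comparison it was sized for.

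**What to change.** Amend the text in four places.

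1. In Design, limit the power statement to each brief intervention against the leaflet.
2. In Sample size calculation, state that BLC v BA was not used to size the trial.
3. In the same section, give the detectable BLC v BA difference as a range over assumed BA rates, with the assumptions shown: for example, about 14–16 points at 10% and 16.5–18 points at 18%.
4. In Planned analysis, state that this contrast will be interpreted by its estimate and 95% CI, and that non-significance will not be taken as no added benefit.

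The cost is wording only. Arms, recruitment, outcomes and the order of the hypotheses stay as they are. The price is an open statement that the trial was not sized for one of its hypotheses.

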### Study Hypotheses

• Brief lifestyle counselling by an Alcohol Health Worker (AHW) is more effective and cost effective than simple structured advice conducted by OMs in a typical probation setting.

• Brief lifestyle counselling and simple structured advice are more effective and cost effective than a Client Information Leaflet (CIL).

• Access to referral to an AHW results in greater screening and intervention activity than training of probation staff in screening and brief intervention alone.

• Attitudinal, practical skill, resource, and reinforcing factors predict screening and intervention activity.

### Probation Office recruitment

Contact with probation offices will initially be made via regional Chief Probation Officers and regional alcohol leads for probation. Thereafter visits to probation offices will be arranged to enable research staff to explain the trial protocol, secure staff consent to participate and to organize the probation office-based training.

### Inclusion Criteria

#### Probation offices

All probation offices that have not already instigated screening and brief intervention systems.

#### Offenders

Any offender with a positive screening result on FAST or M-SASQ, who is alert and orientated aged 18 or over, resident within 20 miles and able to speak, read and write English sufficiently well to complete study questionnaires.

### Exclusion Criteria

Offenders will not be eligible if they are already seeking treatment for an AUD or are taking part in another study of alcohol interventions, if they are severely injured or suffering with a serious mental health problem, or who are grossly intoxicated. Finally offenders with no fixed abode will be excluded from the study.

### Randomisation

Randomisation will be conducted using a secure remote randomisation service. Blocks containing six possible allocations will be generated for each of the permutations of screening method (FAST vs M-SASQ) and intervention (CIL vs BA vs BLC). OMs will be randomly assigned to each allocation en masse at the start of the trial. Randomisation will be stratified by geographical area.

### Screening

In order to test the relative effectiveness of different screening methods in identifying hazardous and harmful drinkers we intend to conduct a cluster randomised comparison of two validated screening tools. A modified version of the M-SASQ which asks "How often do you have X or more standard drinks on one occasion?" where X = 6 for women and 8 for men, with monthly, or weekly, or daily or almost daily considered a positive screen [29]. We tested the M-SASQ in a pilot study and established a sensitivity of 91.8 and specificity of 70.8 when compared to the gold standard Alcohol Use Disorders Identification Test (AUDIT) [27]. FAST [28] is a universal screening tool that has high sensitivity and specificity in health settings ([28]. All screening tools have been modified to include a visual guide to interpreting a 'standard drink'. (A standard drink = 8 mg of pure ethanol = 1 UK Unit of alcohol).

All offenders who are attending probation and potentially eligible will be informed of the study and asked to consent to be screened. They will be screened using the instrument available to the OM. Participants will be informed of the outcome of the screening.

In all conditions, the research team will support participating OMs in implementing screening systems tailored to the needs of the probation office.

